#### 9.7. Managements of random allocation

- When a random assignment table is prepared, it is managed by an independent statistician.
- When the test subjects listen to the explanation of the study and write a consent form for participation in the clinical trial, they are given screening numbers in order.
- Participants who pass the screening test during their first visit will be assigned a registration number and group based on the random assignment table stored by an independent statistician.

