## 5.3. Methods of management and storage of clinical trial drugs

- The clinical trial pharmacist is responsible for the acquisition, storage, preparation, management, and return of drugs used in clinical trials. The clinical trial pharmacist shall confirm in writing the receipts and quantity of clinical trial drugs received, sign them, and manage them appropriately.
- Clinical trial drugs are administered by the clinical trial pharmacist according to the principal investigator's prescription, and the clinical trial pharmacist must accurately record the

Version 2.6

clinical trial drugs and management given to each participant.

- This clinical trial is an open clinical trial, identified by the test subject identification number, and the clinical trial drug prescribed to each test subject and the returned clinical trial drug should be properly recorded.
- When the clinical trial is suspended or terminated, the clinical trial pharmacist must return the unused clinical trial drug to the clinical pharmacy of Kyung Hee University Medical Center and store the return certificate, and the clinical pharmacy of Kyung Hee University Medical Center must discard the returned clinical trial drug.

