## 9. Trial design

### 9.1. Trial design

## Version 2.6

- This study is a prospective, randomized, open-label, parallel-group, multi-center, and controlled trial involving participants from four clinical research centers in Korea. Eligible participants will be randomly allocated to either the experimental or control group after screening based on the inclusion and exclusion criteria. The patients will receive treatment for 12 weeks. The unstimulated and stimulated salivary flow rate (SFR) test, visual analog scale (VAS), salivary scintigraphy, and questionnaires for oral symptoms and quality of life will be assessed for up to 12 weeks after the first visit.

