**9.2. Trial schedule**

| Timepoint
Assessment           | Screening
Period | Treatment period |      |               |      |               |       |                |
|-----------------------------------|---------------------|------------------|------|---------------|------|---------------|-------|----------------|
|                                   | -1w - 0w            | 1w               | 2-3w | 4w            | 5-7w | 8w            | 9-11w | 12w            |
|                                   | V1
(-1w~0d)      | V2
(0w)       |      | V3
(4w±2d) |      | V4
(8w±2d) |       | V5
(12w±2d) |
| Informed consent                  | ●                   |                  |      |               |      |               |       |                |
| Demographics                      | ●                   |                  |      |               |      |               |       |                |
| Medical examination               | ●                   |                  |      |               |      |               |       |                |
| Physical examination              | ●                   | ●                |      | ●             |      | ●             |       | ●              |
| Vital signs                       | ●                   | ●                |      | ●             |      | ●             |       | ●              |
| Blood tests                       | ●                   |                  |      | ●             |      | ●             |       | ●              |
| 12 lead ECG                       | ●                   |                  |      |               |      |               |       |                |
| Random allocation                 | ●                   |                  |      |               |      |               |       |                |
| Pilocarpine          |                     | ●                | ●    | ●             | ●    | ●             | ●     | ●              |
| Baekhogainsa m-Tang  |                     | ●                | ●    | ●             | ●    | ●             | ●     | ●              |
| OHIP-14                           |                     | ●                |      | ●             |      | ●             |       | ●              |
| EQ-5D-5L                          |                     | ●                |      | ●             |      | ●             |       | ●              |

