#### **9.9.2. Visit 2~5 (Week 0~12)**

- Eligible participants are randomly allocated to either the experimental or control group after screening based on the inclusion and exclusion criteria and written informed consent.
- Both experimental and control groups receive 4-week clinical trial drugs every 4 weeks (Before administration (0 weeks, Visit 2), 4 weeks after administration (4 weeks  $\pm$  2 days, Visit 3), and 8 weeks after administration (8 weeks  $\pm$  2 days, Visit 4)).
- The following tests will be conducted at each visit, including before administration (0 weeks, Visit 2), 4 weeks after administration (4 weeks  $\pm$  2 days, Visit 3), 8 weeks after administration (8 weeks  $\pm$  2 days, Visit 4), and 12 weeks after administration (12 weeks  $\pm$  2 days, Visit 5).
  - Assessment of drug compliance and return of unused clinical trial drugs
  - Monitoring adverse events and evaluating concomitant medication
  - Vital signs and physical examination
  - Clinical laboratory examination (hematologic test / biochemical test / urinalysis)
  - Salivary flow rate (SFR) test
  - Evaluation of visual analog scale (VAS) for xerostomia

Version 2.6

- Salivary scintigraphy
- 14-item Oral Health Impact Profile (OHIP-14) questionnaire
- 5-level EuroQol 5-dimensional (EQ-5D-5L) questionnaire

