**10.2.3. Salivary scintigraphy**

- Evaluation at Visit 2 (Week 0) and Visit 5 (Week 12).
- For the objective evaluation of salivary gland function, salivary scintigraphy will be performed after the administration of a radiotracer (Technium-99m pertechnetate).
- After intravenous administration of Tc 99m sodium pertechnetate 370 MBq to patients, images are obtained using a low energy-high sensitivity collimator-type dual-head gamma camera (Philips Forte, Philips Medical Systems).
- Images are obtained 5 min, 15 min, and 30 min after intravenous administration of radiotracer, and front images are obtained in the same way after administration of salivary gland secretion stimulators (lemon candy).
- During the examination, the patient's head is fixed and instructed not to swallow saliva.
- To analyze the scintigraphy images, the counts of the regions of interest (ROI) will be evaluated in the parotid and submandibular glands. Three parameters – uptake ratio (UR), maximum accumulation (MA), and maximum secretion (MS)– will be calculated using the following formulas
- (1) UR is calculated as the salivary gland count – the background count.
- (2) The MA (%) is calculated as follows: (maximum activity before stimulation – initial activity 5 min after radiotracer injection) × 100 / maximum activity before stimulation.
- (3) The MS (%) is calculated as (maximum activity prior to stimulation – activity after stimulation) × 100 / peak activity before stimulation.

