**10.2.4. OHIP-14 (The 14-item Oral Health Impact Profile) Questionnaire**

## Version 2.6

- Evaluation at Visit 2 (Week 0), Visit 3 (Week 4), Visit 4 (Week 8), and Visit 5 (Week 12).
- Subjective quality of life will be evaluated using OHIP-14 Korean version. The responses will be measured on a scale ranging from 0 (never) to 4 (always), generating a total score of 0 to 56 (lowest quality).

| How often do the following situations occur due to a disease in your mouth? |            |             |                   |                 |             |
|-----------------------------------------------------------------------------|------------|-------------|-------------------|-----------------|-------------|
|                                                                             | 0
Never | 1
Rarely | 2
Occasionally | 3
Frequently | 4
Always |
| Problems with pronunciation                                                 |            |             |                   |                 |             |
| Bad sense of taste                                                          |            |             |                   |                 |             |
| Pain                                                                        |            |             |                   |                 |             |
| Discomfort when eating                                                      |            |             |                   |                 |             |
| Concern for the mouth                                                       |            |             |                   |                 |             |
| Self-consciousness due to oral problems                                     |            |             |                   |                 |             |
| Dissatisfaction with food intake                                            |            |             |                   |                 |             |
| Interruption of meals                                                       |            |             |                   |                 |             |
| Difficulty relaxing due to oral problems                                    |            |             |                   |                 |             |
| Embarrassment arising from oral problems                                    |            |             |                   |                 |             |

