##### **13.1.3. Efficacy outcomes**

- Efficacy outcomes will be analyzed for both the per-protocol (PP) and ITT populations. In case of discrepancies between the efficacy outcomes of PP and ITT populations, both set of results will be presented and compared, with the PP population considered the main

Version 2.6

analysis and the ITT population as supplementary analysis.

- The ITT population consists of participants who received at least one dose of the clinical trial drugs and underwent efficacy evaluation more than once during the treatment period. In cases of missing values due to dropouts or discontinuation before the clinical trial ends, missing data from dropout participants will be imputed using the last observation carried forward analysis.
- The PP population is a subset of the ITT population. It includes participants who consumed >70% of the prescribed doses of clinical study drugs and completed follow-up visits and corresponding outcome measurements (weeks 4, 8, and 12) during the 12-weeks treatment periods. Participants falling under a 'significant violation of clinical trial plan' will be excluded from the PP population.

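### Random allocation is scheduled at Visit 1, before the Visit 2 baselines of OHIP-14, EQ-5D-5L and scintigraphy, and this open-label protocol has nothing to keep the arm concealed in between

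*Protocol*

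**What the plan says.** On the time of allocation, section 9.7 states: "Participants who pass the screening test during their first visit will be assigned a registration number and group". The row "Random allocation" is marked only in the Visit 1 column, which runs from one week before to day 0, in the summary schedule and again in the table of section 9.2. Section 9.9.2, headed Visit 2~5, says: "Eligible participants are randomly allocated to either the experimental or control group after screening". That sentence stands before the list of tests for Visits 2 to 5.

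On the baselines, section 10.2.4 (OHIP-14) has "Evaluation at Visit 2 (Week 0), Visit 3 (Week 4), Visit 4 (Week 8), and Visit 5 (Week 12"), and section 10.4 gives the same timing for EQ-5D-5L. Section 10.2.3 (scintigraphy) has "Evaluation at Visit 2 (Week 0) and Visit 5 (Week 12"). For salivary flow and VAS, sections 10.2.1 and 10.2.2 use the screening value as week 0.

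On blinding, section 9.1 reads: "This study is a prospective, randomized, open-label, parallel-group, multi-center, and controlled trial". Section 5.3 adds: "This clinical trial is an open clinical trial, identified by the test subject identification number". Under section 9.8 the first digit of the registration number stands for the group, and that number identifies the subject until the end of the trial.

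A footnote to the summary schedule allows Visits 1 and 2 to be held together once consent is obtained. It gives no order of procedures within the combined visit.

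**The concern.** A baseline should be fixed before anyone can react to the assignment. Here three baselines are scheduled after allocation, in a trial without blinding. The arms differ in a way that invites expectations: the full pilocarpine dose against half the dose plus herbal granules. A patient who knows the arm may answer a quality-of-life questionnaire differently.

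The outcome at stake is OHIP-14. Section 13.3.2.1 lists its difference and its mean percentage change from week 0 to week 12 as secondary outcomes, so the baseline enters both as the value subtracted and as the denominator. Adjusting for baseline does not cure this, because the covariate itself could carry an effect of allocation. The baseline comparison planned in section 13.2 could not detect it either, since a chance imbalance and a reaction to the assignment would look alike. No later analysis can restore a baseline taken after allocation, so the protocol has to settle the order.

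**Working it through.** The protocol gives no figure for this point, so the check sets the sections side by side.

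| Item | When | Where | Relative to allocation at Visit 1 |
|---|---|---|---|
| Group assignment | Visit 1, on passing screening | 9.7; both schedule tables | – |
| Group assignment | after screening, under Visits 2 to 5 | 9.9.2 | visit unclear, but listed ahead of the Visit 2 tests |
| First dispensing | Visit 2 | 9.9.2 | after |
| Salivary flow baseline | screening | 10.2.1; both tables | before |
| VAS baseline | screening | 10.2.2; both tables | before |
| OHIP-14 baseline | Visit 2 | 10.2.4; both tables | after |
| EQ-5D-5L baseline | Visit 2 | 10.4; both tables | after |
| Scintigraphy baseline | Visit 2 | 10.2.3; both tables | after |

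**Order.** Section 9.7 and the tables put the three Visit 2 baselines after allocation. Reading section 9.9.2 as placing allocation at Visit 2 does not help, because allocation still comes first there. No section puts any of the three ahead of allocation.

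**Flow and VAS.** Section 9.9.2 also names these among the tests at each visit from week 0. Sections 10.2.1 and 10.2.2 and the tables take the screening value instead. Both measures are eligibility criteria, so they must precede allocation.

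**Length of the gap.** Section 9.9.1 places screening within 7 days before the first intervention. The gap from allocation to Visit 2 is therefore at most 7 days, and it shrinks to one visit when Visits 1 and 2 coincide.

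**Concealment.** The trial is open, the subject number shows the group (9.8), and no section withholds the assignment until the baselines are complete.

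**How a shifted baseline enters OHIP-14.** Let d be the between-arm difference in mean baseline caused by knowing the arm, and e the same quantity at week 12. Let β be the slope of the week-12 value on baseline.
- Raw change (week 12 minus week 0): bias = e − d.
- Baseline-adjusted comparison: bias = e − βd.

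The protocol gives none of d, e or β. As an illustration only, assume that |d| is 1 to 3 points and e = 0. The raw change contrast then moves by 1 to 3 points, which is 1/56 = 1.8% to 3/56 = 5.4% of the 0–56 scale. Measuring OHIP-14 before allocation makes d = 0 and leaves e as it is.

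**Primary outcome.** Section 13.3.1 uses unstimulated flow at week 12. No Visit 2 baseline enters that comparison.

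**The case against.** The strongest objection is that the protocol fixes when the group is assigned, not when the patient hears of it. A reader might infer that patients are told their arm at Visit 1, but no section says so, and drug is first dispensed at Visit 2. Section 16.5 even asks monitors to confirm that the random number remains blinded, although it is unclear what this means in an open trial. The interval may also be short. Registration numbers follow the date on which screening is passed (9.8), which depends on laboratory results, and the visits may be merged. Section 9.9.2 can be read as agreeing with 9.7, since both place allocation after screening. All of this stands. It turns a claim of known unblinding into one of unprevented unblinding, and it makes 9.9.2 a loose placement more than a flat contradiction.

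Other stronger readings also fail:
- **EQ-5D-5L.** A reader might expect biased EQ-5D-5L change comparisons. The instrument is not in the secondary list of section 13.3.2.1, and section 10.4 keeps it for later economic work.
- **Scintigraphy.** Its parameters are computed from gamma counts by set formulas (10.2.3). No blinded reading is described, but it is hard to see how a patient's expectation would move them.
- **Size.** A reader might take the OHIP-14 bias to equal the baseline shift exactly. That holds only for a raw change score with no shift at week 12. Week-12 answers are open-label too, and shifts in the same direction would partly cancel.
- **Analysis set.** The ITT population is limited to "participants who received at least one dose of the clinical trial drugs" who also have efficacy evaluations during treatment. A reader might infer that the gap before dosing lets arm-driven exclusions in, to be cured by later allocation. The protocol gives no evidence of such exclusions, and the requirement for on-treatment evaluation would remain after the change.

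**Conclusion.** The point holds as a matter of sequence. Followed as written, the protocol allocates before the baselines of OHIP-14, EQ-5D-5L and scintigraphy, and nothing prevents the arm from being known when they are taken. The outcome chiefly exposed is the change in OHIP-14, a self-reported secondary outcome. EQ-5D-5L is exposed to a lesser extent, through its later economic use, and scintigraphy is little exposed.

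The size of any bias is unknown, and the 1 to 3 points above are an assumption. Bias arises only if patients do learn the arm before answering and if that knowledge alters their answers; the protocol establishes neither. The week-12 primary outcome, the non-inferiority conclusion drawn from it, and the flow and VAS baselines are not affected. The change is worth making because it costs almost nothing, not because a main result is in danger.

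**What to change.** Schedule allocation at Visit 2, after OHIP-14, EQ-5D-5L, scintigraphy and every other baseline measurement are complete, and immediately before dispensing. State that the same order applies when Visits 1 and 2 are held together. Then reconcile the text: amend section 9.7, so that passing screening leads to eligibility but not yet to a group; move the allocation sentence in section 9.9.2 behind the Visit 2 baseline tests; and move the allocation mark to Visit 2 in the summary schedule and in the table of section 9.2. Since the registration number in section 9.8 shows the group, it should be issued at the same moment.

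No extra visit, patient or procedure is needed. The one practical cost is that allocation and drug preparation have to be done on the same day as the Visit 2 assessments, scintigraphy included.

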## 9.8. Test subject number

- A screening number is assigned to the test subjects who have agreed to participate in the clinical trial in the order of time of written informed consent. The screening number starts with KH-S001, and the rest, excluding KH-, consists of four digits in total and three numbers (Kyung Hee University Medical Center 'KH-', Inha University Hospital 'IH-', Myongji Hospital 'MJ-', and Kyung Hee University Hospital at Gangdong 'KD-'). Finally, test subject number (registration number) is assigned in order of the data the screening passes were determined (in the order of the time of informed consent if the same date) and assigned to the group according to a pre-written random assignment table. The test subject identification number starts with each KH-R1001, and the rest, excluding KH-, consists of five digits and four numbers (Kyung Hee University Medical Center 'KH-', Inha University Hospital 'IH-', Myongji Hospital 'MJ-', and Kyung Hee University Hospital at Gangdong 'KD-'). The identification number shall be assigned as follows. One (or two) of the first number is assigned to the group, and the last three numbers are assigned in the order of random assignments. The screening number and test subject identification number assigned to each test subject are used as codes to recognize the test subject until the end of the clinical trial.

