### **15.3. Confidentiality**

- All records that can identify the test subject must be kept confidential. All documents related to clinical trials, such as CRFs, are recorded and classified by the subject identification code (subject number, initials) rather than the test subject's name to protect the subject's privacy and ensure the confidentiality of the record, and if there is a subject's name in the medical record (pathological report, video record, etc.), it shall be deleted and stored. Even when the results of the clinical trial are published, the identity of the test subject will remain confidential, and only the subject number or initials will be recorded if the subject's individual data must be published or reported.
- Clinical trial monitoring personnel and inspectors, as well as the Ministry of Food and Drug Safety and the clinical trial review committee, can access the subject's medical records for the purpose of confirming the collected information. At this time, the information of the subject to be exposed will be handled under thorough confidentiality, and the investigator will inform the subject of this fact.

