**16.3. Ensuring data quality and data security**

- Before the start of the clinical trial, an initiation meeting is held in which investigators participate. In this meeting, detailed discussions will be held on the research plans, research conduction, CRFs, sample collection and pre-processing methods. Monitoring personnel monitor according to the monitoring plan.
- The clinical trial coordinator and monitoring personnel shall double-check all data recorded in the CRF. If abnormalities are found, compare and review with the supporting documents. The data entered in the CRF should be double-checked according to the trial institution's Standard Operating Procedure (SOP) and data management plan. When data input is

Version 2.6

confirmed, lock the database system.

- The query list for unresolved queries should be resolved with the investigator through clinical trial monitoring personnel. The database is modified based on signed query resolution.
- Security should be maintained for all documents such as supporting documents and CRFs obtained through the clinical trial, and investigators should not disclose such information without the consent of the sponsor.
- Since the anonymity of the test subjects must be guaranteed, the test subject number or initials are used in all documents instead of the test subject's name. Documents that can identify test subjects should also be secured by the investigator.

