## Version 2.6

- Monitoring of clinical trials will be conducted through regular test subjects' visits and phone calls by monitoring personnel of the Oriental Medicine Clinical Trial Center at Kyung Hee University Korean Medicine Hospital, which has been entrusted with the task. During the visit, the monitoring personnel should basically check the original patient record, drug management record, and data storage (study file), and confirm that the blindfolding of the random number allocated for each subject's unique code is maintained. In addition, the monitoring personnel carefully examines the progress of the clinical trial and consults with the investigator if there is a problem.
- The appropriate time for these visits shall be allocated by consultation between the investigator and the monitoring personnel. The investigator shall also allow the monitoring personnel to view the original documents (such as hospital or individual charts, laboratory result records, appointment records, etc.) of the test subjects, as defined in the Korean Good Clinical Practice (KGCP).

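### The subject number carries the treatment arm as its first digit, which can needlessly reveal the arm to the scintigraphy reader and does not fit the blinding check asked of monitors

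*Protocol*

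**What the plan says.** Section 9.8 gives each participant two codes. The screening number (KH-S001 format) follows the order of consent. The identification number follows later, when the participant is "assigned to the group according to a pre-written random assignment table". On its format the section says "The test subject identification number starts with each KH-R1001", and then: "One (or two) of the first number is assigned to the group, and the last three numbers are assigned in the order of random assignments". Both codes "are used as codes to recognize the test subject until the end of the clinical trial".

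Two sections say where the code is used. Under Section 15.3, trial documents such as CRFs "are recorded and classified by the subject identification code (subject number, initials) rather than the test subject's name". Under Section 16.3, "the test subject number or initials are used in all documents instead of the test subject's name".

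Section 10.2.3 describes the scintigraphy reading: "the counts of the regions of interest (ROI) will be evaluated in the parotid and submandibular glands". UR, MA and MS are calculated from these counts, and UR also subtracts a background count. No reader, blinding or reading code is named.

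Section 5.3 calls the trial open. Section 16.5 nevertheless has monitoring personnel "confirm that the blindfolding of the random number allocated for each subject's unique code is maintained".

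**The concern.** Open treatment does not require open measurement. Scintigraphy images can be analysed away from the clinic, under a label that says nothing about treatment. If the label is the identification number, that option is lost, because the first digit gives the arm.

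What is at stake is the change from week 0 to week 12 in UR, MA and MS, listed as secondary outcomes in Section 13.3.2.1. Where an operator chooses the regions and the background, knowing the arm can move the counts in either direction.

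Separately, monitors are given a check which, read as it is worded, cannot be met for the group once the number has been issued.

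**Working it through.** There is no figure in the plan to reproduce, and no arithmetic applies. The check sets the sections side by side.

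1. **Does the first digit mark the randomised arm?** Section 9.8 speaks of the group that comes from the random assignment table, and the digit is tied to that group. With two groups and a digit of 1 or 2, R1xxx and R2xxx separate the arms. The protocol does not say which arm is 1, but in an open trial that is soon known.

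2. **Does the number reach people who read outcomes?** Sections 15.3 and 16.3 prescribe the number or initials for trial documents. Neither says which is put on images or on region-of-interest result forms. The number may be used there, and nothing rules it out.

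3. **Does the number exist when the images are read?** The schedule places random allocation at Visit 1 and scintigraphy at Visit 2 (week 0) and Visit 5 (week 12). Section 9.7 issues the registration number to participants who pass screening at the first visit. Both the baseline and the final image can therefore carry it.

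4. **Would another label keep the reader masked?** Section 10.2.3 works from counts on acquired images. Computing them needs neither the patient nor the drug. A neutral label would therefore remove a route by which the reader learns the arm.

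5. **Is a neutral label available?** Yes. The screening number is given before allocation, has no group digit, and is kept as a valid code to the end of the trial.

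6. **Does Section 16.5 fit with the rest?** Section 5.3 declares an open trial identified by the subject number, and Section 9.8 puts the group into that number. Section 16.5 asks for confirmation, subject by subject, that the random number behind the code is still blinded. As worded, these three sections do not agree.

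**The case against.** The strongest reply is that the trial is openly declared open-label and nowhere promises blinded readers, so a readable arm is consistent with its design. That stands: a cheap safeguard is forgone, but no commitment is broken. It also stands that Sections 15.3 and 16.3 allow initials and that no reader is named. The effect on the scintigraphy reader is therefore an inference.

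Section 16.5 can also be read as concealment of the allocation list, which Section 9.7 leaves with an independent statistician. That reading is possible, but the sentence is written per subject code and should say so if that is what it means.

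A reader might infer more than the protocol supports:

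- **That the primary saliva outcome is biased by the number.** Section 9.9.2 puts the salivary flow test in the same visit as the compliance check and drug return. Section 10.5 counts returned tablets and empty packaging, and only the experimental arm receives granules (Section 9.3). The participant is present and knows the treatment. A new number format would not blind this step, and the protocol gives no basis for assuming any particular error in reading saliva volume.
- **That those who check the data would otherwise be blind.** Section 16.1 has the CRF document receipt of trial drugs, and the individual adverse event listings in Section 13.4.1.1 include the group.
- **That the number is on every document.** The text says number or initials.
- **That the digit breaks allocation concealment.** The number is issued at allocation, so the digit does not by itself reveal the next assignment.

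**Conclusion.** The point holds in a limited form, and its severity is minor. The identification number carries the arm without need. It can thereby show the arm to the person who performs an operator-dependent reading of secondary outcomes. Section 16.5 also needs to be reconciled with Sections 5.3 and 9.8.

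No numerical size can be given, because the protocol has no data on how far scintigraphy counts vary with region placement. The non-inferiority test in Section 13.3.1 uses unstimulated salivary flow and is not touched.

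The conclusion rests on three assumptions: that regions and background are set by an operator and not by a fully automatic routine; that images or result forms would carry the identification number; and that the reader does not already know the arm from contact with the patient. If any of these fails, the gain from relabelling shrinks or disappears. The conflict over the wording of Section 16.5 remains in any case.

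**What to change.** - **Section 10.2.3:** label scintigraphy images and region-of-interest result forms with the screening number only, for enrolled and new participants. Have the usual reader record the counts under that code before any link to arm is made.
- **Section 9.8:** drop the group digit from newly issued registration numbers. The text does not say whether the last three digits run within an arm or across both, so the new numbers should run in one sequence across arms and not collide with any already issued. Do not renumber enrolled participants: changing identifiers in the e-CRF, pharmacy and source records risks mismatches, and the screening number makes it unnecessary.
- **Section 16.5:** replace the present check with two that can be met, namely that the unissued part of the allocation list is still concealed and that scintigraphy labels do not show the arm.

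The cost is a small labelling change and a cross-reference list between screening and registration numbers. No additional reader, visit or examination is needed. The only new discipline is the order of recording: counts first, link to arm afterwards.
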